### Interim analyses {21b}

The principal investigator will decide to suspend the study if any serious adverse event is reported until the cause is identified. If it is verified that the event was not related to the medical device, the study will restart under sponsor permission. However, if the cause of the serious adverse event is related to the investigational device and the investigation is terminated, the interim results will be accessed by the principal investigator, that will perform the correspondent analysis.

### Methods for additional analyses (e.g., subgroup analyses) {20b}

Not applicable; all the analyses are already described in the study protocol.

### Methods in analysis to handle protocol non-adherence and any statistical methods to handle missing data {20c}

This study needs 20 participants to conclude the statistical analysis of the primary endpoint. Then, a new participant will be recruited whenever there is any dropout or loss of follow-up until the collection of the biopsy of 20 participants.

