### Trial design {8}

This protocol refers to a randomized superiority trial. This is a prospective, open, single-center, positive-controlled study, with two parallel groups, assigned as a split-mouth model, whereupon each side of the mouth will be allocated as an independent unit and each patient will receive both treatments, test and control.

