### Criteria for discontinuing or modifying allocated interventions {11b}

Criteria were not applied because the study will evaluate a medical device in a split-mouth allocation; therefore, it is impossible to change the allocation once the device is installed. The patient will be discontinued from the study only if they experience a serious adverse event, which can be correlated with the device. So far, we have foreseen a serious allergic reaction to the device material and a serious infection.

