### Sample size {14}

Sample calculations were performed based on tomographic bone formation data from the study, which evaluated the volumetric stability of autogenous and allogeneic corticomedullary block grafts used for volume increase associated with edentulous alveolar ridges [19]. This choice was due to the lack of studies comparing β-tricalcium phosphate blocks and autogenous bone and the similarity of the methodology for evaluating the stability of block grafts. As a result, it was verified that the minimum difference between the means of treatments concerning the percentage of volumetric reduction of the graft was 11.90, with a standard deviation of 12.09. Therefore, considering a study power (1-β) of 0.8 and an *α* power of 0.05, a minimum sample of 20 participants was determined, each of whom will receive two grafts, one synthetic in a personalized block and another in an autogenous block. To maintain the power of the study, the sample size should be maintained, thus if any participant dropout or is discontinued before the analysis of the primary outcome, a new participant will be recruited instead, until complete 20 participants.

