## Statistical methods

### Statistical methods for primary and secondary outcomes {20a}

Data from this study will be analyzed for their distribution by the Shapiro-Wilk normality test. If the data are distributed according to normality, parametric tests will be used for the inferential analysis of the data. The comparison between groups in each experimental period will be performed using the unpaired *t*-test. The longitudinal evaluation of these data within each group will be evaluated using the ANOVA test for repeated samples complemented by the Tukey test. If the data are not distributed according to normality and the qualitative parameters, they will be analyzed inferentially using non-parametric statistical tests. The comparison between groups in each experimental period will be performed using the Mann-Whitney test. The longitudinal evaluation of these data within each group will be evaluated using the Friedman test complemented by the Dunn test. The BioStat software version 5.3 will be used to perform the statistical analysis of this project.

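### Patients discontinued for a serious event linked to the test device are replaced, with no matching discontinuation rule for the autograft, so the primary volume comparison can be biased towards the test graft

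*Protocol article*

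**What the plan says.** Four sections of the protocol article act together.

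- **Criteria for discontinuing or modifying allocated interventions {11b}:** "The patient will be discontinued from the study only if they experience a serious adverse event, which can be correlated with the device". Serious allergic reaction to the device material and serious infection are the events foreseen. No equivalent ground is given for the autograft.
- **Sample size {14}:** "if any participant dropout or is discontinued before the analysis of the primary outcome, a new participant will be recruited instead", continuing until 20 are complete.
- **Methods in analysis to handle protocol non-adherence and missing data {20c}:** the only method given is that "a new participant will be recruited whenever there is any dropout or loss of follow-up until the collection of the biopsy of 20 participants".
- **Item {18b}, on participant retention:** data already collected are used, but only for the steps the participant completed.

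Under Volumetric analysis, the volume outcome compares the scan after grafting with the scan eight months later. Under Interim analyses {21b}, the principal investigator suspends the study after a serious adverse event until the cause is identified, and termination is contemplated if the device is the cause. On the hypothesis, Trial design {8} states: "This protocol refers to a randomized superiority trial".

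**The concern.** Replacement restores the count of 20 but not the set of patients who were randomised. If a patient leaves because of what the test graft did, and a new patient takes the place, the primary comparison is made among patients in whom that event did not occur. In a split-mouth trial both grafts leave together, but this does not cancel the problem: the lost pairs are those in which the test side is likely to have done badly, so their absence moves the contrast.

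The protocol-directed withdrawal is tied to one of the two treatments. A comparable serious event on the autograft side does not trigger it, so that pair can stay in with its poor control result. In an open superiority trial of the sponsor's own device, this could contribute to a finding of superiority that would not hold if every grafted patient counted.

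**Working it through.** **1. The plan's own figure.** Sample size {14} gives a difference and SD for "the percentage of volumetric reduction of the graft was 11.90, with a standard deviation of 12.09", with "considering a study power (1-β) of 0.8" and alpha 0.05. Two-sided testing and a per-graft SD are assumed, since neither is stated.

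- Normal approximation: n = 2 × (1.960 + 0.842)² × (12.09/11.90)² = 2 × 7.849 × 1.032 = 16.2, so 17 per group.
- Exact unpaired t: 18 per group (power 0.818). At 20 per group, power is 0.858.

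The stated 20 is therefore adequate. The issue is bias, not sample size.

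**2. What happens to each kind of patient before month 8**

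| Event | Consequence under the text |
|---|---|
| Serious event correlated with the test device | Discontinued {11b}, replaced {14}; no 8-month volume for {18b} to retain |
| Serious event from the autograft only | No protocol-directed discontinuation; pair can stay |
| Voluntary dropout or loss to follow-up, any cause | Replaced {14, 20c} |
| Graft lost, patient stays and is scanned at month 8 | Neither dropout nor discontinued; volume can be analysed |

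Only the first row is both directed by the protocol and specific to one graft.

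**3. Size of the shift.** Let f be the share of test grafts removed, L their volume loss and m the mean loss in the remaining test grafts. Dropping them lowers the apparent test loss by f × (L − m). The documents give none of these values. Assuming m = 20 to 30% and L = 60 to 100%:

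- f = 5%: from 0.05 × (60 − 30) = 1.5 to 0.05 × (100 − 20) = 4.0 points.
- f = 10%: from 3.0 to 8.0 points.

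Against the planned 11.90, the extremes are 1.5/11.90 = 13% and 8.0/11.90 = 67%.

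**4. Effect on the test.** The analysis section {20a} states: "The comparison between groups in each experimental period will be performed using the unpaired" t-test. Assume equal true mean loss of 25% with failures counted as 100%, no autograft failures, every test failure withdrawn and replaced, and SD 12.09. The remaining test grafts then have mean (25 − 100f)/(1 − f).

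- f = 5%: 20/0.95 = 21.05, an apparent advantage of 3.95 points.
- f = 10%: 15/0.90 = 16.67, an apparent advantage of 8.33 points (70% of 11.90).

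The standard error is 12.09 × √(2/20) = 3.823, giving noncentrality 1.03 and 2.18. The critical value on 38 degrees of freedom is 2.024. Chance of a significant result favouring the test graft (exact at correlation 0; simulated with 200,000 trials otherwise):

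| Test failure rate | Correlation 0 | 0.3 | 0.5 |
|---|---|---|---|
| 5% | 17% | 13% | 10% |
| 10% | 57% | 58% | 59% |

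The nominal rate in that direction is 2.5%. With an equal true mean of 30% instead and correlation 0, the figures are about 15% and 50%. When all randomised patients are kept in that 30% setting and failures are scored 100%, the rate is about 5.5 to 7%. Most of the excess therefore comes from dropping the failures, though a small excess remains because the scored data are skewed.

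**The case against.** Several objections have force.

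- **Suspension.** Interim analyses {21b} provides for the study to be suspended after a serious adverse event and possibly ended if the device is at fault. A steady run of replaced device failures presupposes that the trial resumes each time. At failure rates of 5% and 10%, the chance of at least one among 20 patients is 1 − 0.95²⁰ = 64% and 1 − 0.90²⁰ = 88%, so this clause would matter. Termination is not automatic, however, and nothing in the clause returns a withdrawn patient to the analysis. It limits the size and leaves the mechanism.
- **Direction.** All dropouts are replaced, including any caused by donor-site morbidity or autograft failure, and these can bias the other way. A reader might infer that missingness runs in one direction only. The text supports that only for the protocol-directed withdrawal.
- **Reach.** A reader might infer that anyone without a biopsy is replaced, or that all test-graft failures vanish. Item {20c} is triggered by dropout or loss to follow-up, and 20 biopsies is the stopping count. A failed graft in a patient who stays and is scanned can be analysed, and serious device-correlated events are narrower than graft failures in general.
- **Two rules.** Items {14} and {20c} count to 20 in different terms, but the scan and the biopsy fall at the same 8-month milestone, so the difference is minor.
- **Analysis plan.** Analysis sets and failure scoring are often left to a statistical analysis plan, which is not shown. The discontinuation and replacement rules, however, are stated in the protocol, and a later plan cannot recover 8-month data never collected from discontinued patients.

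**Conclusion.** The concern holds in limited form. As written, the rules selectively remove and replace pairs affected by serious events correlated with the test device, with no counterpart for the autograft, and this can bias the primary volume comparison towards the test graft. That the affected test grafts would have shown poor volume is an inference, more plausible for serious infection than for every allergic reaction.

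The net size is unknown. The 57 to 59% and 10 to 17% figures rest on assumed failure rates, no autograft failures, withdrawal and replacement of every failure, and a 100% loss score, none of which is in the documents. In that example the surviving test grafts really do lose less volume, so calling the result false superiority depends on counting failures as loss.

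Higher figures, 69 to 83% at a 10% failure rate and 22 to 28% at 5%, arise with a paired t-test at correlations 0.3 to 0.5. They do not describe the unpaired test the protocol plans and should not be cited for it.

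**What to change.** - **Sample size {14} and missing data {20c}:** state that all randomised and grafted patients remain in the primary analysis set, and that replacements are added without displacing them.
- **Discontinuation {11b} and retention {18b}:** state that discontinued patients continue in data collection, and that the 8-month volume of both sides is analysed wherever a scan is available.
- **Statistical methods {20a}:** prespecify one rule, applied equally to both sides, for how a graft lost before month 8 counts in the volume outcome (for example complete loss or worst rank). Add a completers-only sensitivity analysis and report graft failures by graft type.

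The cost is protocol wording and one scoring rule. Trial status describes recruitment as still ahead, so the change can precede data collection. The downside is that the test-graft estimate may be less favourable and the variance larger. On numbers alone there is some room: 18 per group inflated for 10% loss is 18/0.90 = 20, although this does not allow for added variance from scored failures.

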### Plans to give access to the full protocol, participant level-data, and statistical code {31c}

Not applicable; only the principal investigator, the research team, the sponsor, and the Brazilian National Health Surveillance Agency (ANVISA) will access participant-level datasets and statistical code.

## Oversight and monitoring

### Composition of the coordinating center and trial steering committee {5d}

The communication will be directly between the sponsor team, the principal investigator, and the coordinating investigator via telephone, e-mails, and internet meetings, following sponsor security protocol. A trial steering committee composed of the sponsor scientific board will constantly follow the trial progress by the electronic CRFs answers.

### Composition of the data monitoring committee, its role and reporting structure {21a}

The study monitoring will be performed by the sponsor, during 3 moments of the study: in the initiation, during the test device installation stage, and during the dental implant installation phase. In addition, an audit visit will be carried out shortly after the installation of the devices to verify data accuracy, completeness, traceability, and delays.

### Adverse event reporting and harms {22}

Adverse effects will be registered in the case report form and by phone call if the event were classified as serious by the principal investigator. According to the severity level of the event, the necessary actions will follow RDC 548/2021 of Brazilian Health Regulatory Agency (ANVISA) [20] obligations and recommendations.

### Frequency and plans for auditing trial conduct {23}

The audit monitoring visit will be conducted by the sponsor at least once during the clinical investigation, in the stitch removal phase after graft installation (3rd visit of the participants) or whenever the sponsor understands that there are severe or repeated Protocol deviations, or when there is suspicion of fraud when requested or suggested by a regulatory authority.

### Plans for communicating important protocol amendments to relevant parties (e.g., trial participants, ethical committees) {25}

Protocol amendments will be communicated to ANVISA. If they are substantial and directly reflect on subjects’ participation, they will be resubmitted to the same ethics committee that approved the study and then submitted to ANVISA for protocol amendment. Non-substantial amendments will be reported in the annual report which must be submitted to ANVISA.

### Dissemination plans {31a**}**

An annual report will be elaborated and submitted to ANVISA. After data analysis, the research will publish the results in an appropriate indexed life science journal. Participants will be communicated the results via e-mail or WhatsApp.

## Discussion

A range of particulate bone grafts is currently available on the market, which is clinically effective and predictable. However, the granules have limitations for adequate rehabilitation/reconstruction of the anatomical structure for complex geometry reconstructions. These bone reconstructions related to complex geometries sometimes require more than one surgical procedure to achieve the desired bone reconstruction: consequently increasing the cost of patient rehabilitation and often delivering a limited result. In the case of extensive reconstructions of bone volume, these grafts need to be associated with screws, meshes, and membranes.

Synthetic grafts are usually ceramic based on calcium phosphates, such as HA, β-TCP, or an association of both [21]. The β-TCP has been highlighted as a material of bone graft substitutes due to its resorption by cells, usually osteoclasts, which end up causing slight local acidification, which leads to the dissolution of β-TCP [22–24]. This process makes the β-TCP a resorbable compound, allowing a rapid replacement by new bone [23, 25, 26]. In addition, bioceramic β-TCP can be obtained through various production methods. One of these processes, additive manufacturing or 3D printing, has been drawing attention thanks to numerous advantages arising from the production method.

Applications of the additive manufacturing process in medicine have been reported since 1994, which have led to the development of personalized implants for the precise reconstruction of bone structure [27, 28]. There are several advantages of additive manufacturing over conventional manufacturing processes, such as control of the porosity and roughness of the blocks (printed parts), complete control over geometry, the possibility of creating structures with interconnected pore systems, precise details of anatomy, low material waste, production of several pieces at once, ability to create sophisticated details and complex internal geometries, high design fidelity, process reliability, and high reproducibility [27–29]. Thus, osteoconductive grafts manufactured by additive manufacturing may provide an alternative solution for the reconstruction of significant bone defects and rehabilitation of patients with severe craniofacial bone atrophy, such as early dental loss, congenital malformation, or after resection of cysts and tumors [30]. Clinical studies using 3D ceramic frameworks for bone regeneration have already been carried out and have shown satisfactory results (9,10,12,14), which ensure their clinical applicability. Furthermore, a recent systematic review [31] evaluated the effectiveness of synthetic blocks for bone augmentation in preclinical studies. As a result, the authors concluded that synthetic blocks are a viable alternative for bone regeneration. However, more clinical studies need to be conducted to confirm the effect of these synthetic blocks on bone neoformation. Thus, the protocol presents a randomized split-mouth clinical study that aims to evaluate the performance and safety of block ceramic bone grafts composed of patient-specific β-TCP for bone augmentation of anterior maxillae.

### Trial status

This is the second version of the protocol. This protocol is approved by ANVISA (for regulatory compliance), and the study will start to recruit the participants in February.

## Data Availability

The sponsor, principal investigator, the research team, and ANVISA (Brazilian Health Regulatory Agency) will access the final data set.

## Abbreviations

β-TCP: β-tricalcium phosphate
ANVISA: National Health Surveillance Agency (Brazilian Health Regulatory Agency)
BBT: Bone area between turns
BIC: Bone-implant contact
BMP-2: Morphogenetic protein 2
CBCT: Cone beam computed tomography
CONEP: National Research Ethics Commission
DICOM: Digital Imaging and Communications in Medicine
HA: Hydroxyapatite
ISQ: Implant stability coefficient
LGPD: General Law of Data Protection
OCN: Osteocalcin
REBEC: Brazilian Clinical Trials Registry
RFA: Resonance frequency analyses
VEGF: Vascular endothelial growth factor
UNESP: São Paulo State University
